**12. Expected AE and Precautions**

**12-1 General precautions**

(1) This product is sterilized, and its sterilized status must be maintained. Do not use products that have passed the expiration date.

(2) Check the contents before use. And the investigational device shall not be used when the damage of container and package or the presence of moisture is discovered.

(3) The surgeon shall remove the extra liquid of Guardix SG using the aspirator before applying the solution of Guardix SG onto the surgical site.

**12-2 Handling Precautions**

(1) The solution of Guardix SG shall be stored and used at the room temperature.\

(2) The solution of Guardix SG can be used in gel state changed after warming it to body temperature.

(3) Guardix SG shall be sterilized and shall not be used after be re-sterilized.

(4) The remaining solution shall be discarded and shall not be reused since it is for single use.

**12-3 Contraindications**

(1) Contraindicated patients

a. Patients whose surgical site is infected or contaminated.

b. Patients who are hypersensitive to GUARDIX SG

(2) Administration with care

a. The safety and efficacy of GUARDIX SG in its use together with other adhesion prevention products has not been confirmed in animal experiments.

b. It is not recommend to use the solution of Guardix SG during the pregnancy.
It is recommended to plan the pregnancy until the complement of first menstrual period after use of Guardix SG’s solution.

**12-4 Expected adverse events when using the anti-adhesive agent**

Infection: Fever and increase in WBC, Allergic reactions: Systemic rash, dyspnea, and edema, Pain, Inflammation

* Guardix SG (Anti-adhesion) is to prevent the adhesion having a physical barrier in order for the fibroid tissue to infiltrate to the damaged tissue. We recorded the degree of adverse events ranging from mild, moderate, and severe depending on the patient and the state since its degree is diverse regardless of same symptom.

(1) Mild: The degree of adverse events is mild.

(2) Moderate: The degree of adverse events is moderate.

(3) Severe: The degree of adverse events is severe.

**12-5 Expected adverse events during and after the surgery**

Bleeding, infection on wound, necrosis of skin flap, Reduction of shoulder joint’s movable range, annular syndrome on breast, seroma, nerve damage and paresthesia, lymphedema, pain and discomfort in neck, back, and arm, tightening feeling in the skin of surgical site

**12-6 Expected AEs in association with anesthesia are as follows**

Liver toxicity, Kidney toxicity, oliguria, urorrhagia, myoglobinuria, Low blood pressure, high blood pressure, brachycardia, tachycardia, blood pressure change, arrhythmia, abnormal EKG, decreased cardiac output, ventricular extrasystole, supraventricular premature beat, atrial premature contraction, atrioventricular block, bigemina,, Coughing, respiratory disorders, apnea, asthma, hypoxia, laryngospasm, Hyperthermia, hypothermia, and malignant hyperthermia, Anxiety, dizziness, spasmodic movements, agitation, derangement, muscular stiffness, Vomiting, nausea, shivering, and headaches, Allergic reactions such as anaphylactic and anaphylactoid reactions, WBC increase, WBC decrease and temporary blood glucose increase, Muscle aches, feeling of listless, CPK increase

**13. Procedure of drop-out and withdrawal**

When the subject stops to participating in or is dropped out from the clinical trial, the result collected from the discontinued date until the time her discontinuation is handled as a withdrawal will be reviewed during the final evaluation if the result’s item can be used for evaluation.

**13-1 Suspension Criteria**

The sponsor considers continuation or suspension of the clinical trial in a part or all of the institutions according to the protocol if the following events develop.

(1) Investigators can discuss with the sponsor to suspension a part or all of the clinical trial considering the developments observed during the study period, and if necessary, a part or all of the clinical trial process can be discontinued by investigators.

(2) Can suspension a part or all of the clinical trial based on safety or management reasons.

(3) If undesirable developments are observed during the study period, investigators are required to make a request to the IRB to suspension the clinical trial. The clinical trial can be suspension according to the decision from the IRB.

(4) The clinical trial can be suspension if the institution cannot cope with the necessity of modifying the protocol.

(5) The clinical trial can be suspension if cannot accept the modification order from the head of the institution, which was based on IRB opinions.

(6) The clinical trial can be suspension if the institution head is ordered to suspension the clinical trial according to IRB opinions.

(7) The clinical trial can be suspension if the institution seriously or continuously offends the KGCP, protocol, or clinical trial contract.

**13-2. Process of Suspension**

(1) If decides to suspension the clinical trial, his/her intention and reasons of decision must be promptly notified to the institution head in writing.

(2) Upon receiving the suspension notification from the sponsor, the institution head must convey the intention and reasons to the PI and IRB in writing.

(3) Upon receiving the notification of suspension from the sponsor via the institution head, the PI must promptly notify subjects of the meaning of suspension, and guarantee appropriate treatment and follow-up measures.

(4) In the case of suspension, subjects are treated according to the protocol.

(5) If the PI terminates the clinical trial early or temporarily suspension the clinical trial without an agreement with the sponsor, the PI must immediately inform the sponsor and IRB, then submit the details in writing.

(6) If the IRB determines early termination or temporary suspension, the PI must inform the sponsor immediately, and submit details of early termination and temporary suspension in writing.

**13-3. Withdrawal**

Registration means a random assignment (receipt of subject number) of subjects who participated in this clinical trial. Dropped out means a subject who was applied with the investigational medical device at least once, but he/she could not complete the clinical trial process due to any reason.

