**H_0_ : D ≤ 10 H_1_ : D〉10 (D=Experimental group(EG) ROM Mean – Control group(CG) ROM Mean)**

* Basis of Calculation: Assumptions for estimating the effective subject number.

① Significance level α = 0.025

② The EG estimation number is 1 time that of CG.

③ Type 2 error (β) is 0.1, and statistical power 90% is maintained.

④ The difference in the average value between two groups: 10 degree.

[figure not shown]

[figure not shown]

[figure not shown]

| Power | N1/N2 | Equivalence Margin  (E) | Actual  Difference  (D) | Significance  Level  (Alpha) | Beta | Standard  Deviation1  (SD1) | Standard  Deviation2  (SD2) |
| --- | --- | --- | --- | --- | --- | --- | --- |
| 0.90022 | 23/23 | 5 | 10 | 0.025 | 0.09978 | 5 | 5 |
| 0.80044 | 17/17 | 5 | 10 | 0.025 | 0.19956 | 5 | 5 |
| 0.90004 | 86/86 | 5 | 10 | 0.025 | 0.09996 | 10 | 10 |
| 0.80003 | 64/64 | 5 | 10 | 0.025 | 0.19997 | 10 | 10 |
| 0.90022 | 191/191 | 5 | 10 | 0.025 | 0.09978 | 15 | 15 |
| 0.80044 | 143/143 | 5 | 10 | 0.025 | 0.19956 | 15 | 15 |
| 0.91250 | 23/23 | 10 | 15 | 0.025 | 0.08750 | 5 | 5 |
| 0.80704 | 17/17 | 10 | 15 | 0.025 | 0.19296 | 5 | 5 |
| 0.90323 | 86/86 | 10 | 15 | 0.025 | 0.09677 | 10 | 10 |
| 0.80146 | 64/64 | 10 | 15 | 0.025 | 0.19854 | 10 | 10 |
| 0.90022 | 191/191 | 10 | 15 | 0.025 | 0.09978 | 15 | 15 |
| 0.80044 | 143/143 | 10 | 15 | 0.025 | 0.19956 | 15 | 15 |

Suppose that the 10% subject is dropped out in the middle of trial, the necessary total subject is 192 persons composing of 96 persons for the experimental group and 96 persons for the control.

| Target subject number | EG | CG | In total subject number |
| --- | --- | --- | --- |
| Subject number for final efficacy evaluation | 86 | 86 | 172 |
| Subject number in consideration of drop-out rate (10%) | 96 | 96 | 192 |

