**10.2 Comparator device**

The Comparator device referred as an inactive control isn’t used in this clinical trial.

[Currently, it is uncommon to apply the anti-adhesive agent onto the surgical site of patient who underwent the modified radical mastectomy or breast preservation surgery and the axillary lymph node dissection and it is safe to apply nothing to the surgical site. Therefore, we couldn’t find the reference medical device and didn’t assigned any medical device as the control.]

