**10.3 Methods of Clinical Trial**

(1) Clinical Trial Design

The eligibility evaluation is conducted with the subject who underwent the modified radical mastectomy or breast preservation surgery and the axillary lymph node dissection at Asan medical center and signed at the consent form voluntarily subsequent to the screening test. The subject who isn’t included in the exclusion criteria visits the hospital on the operation day and undergoes the modified radical mastectomy or breast preservation surgery and the axillary lymph node dissection. Then, the subject is assigned to the investigational group or control according to the random assignment slip.

 EG: Guardix SG

 CG: Not applicable

That means the investigational device will be or won’t be applied onto the surgical site of subject depending on her group. Since the investigational device is applied inside of subject in the middle of surgery under anesthetic, the subject is unaware of treatment’s detail.

The related tests will be performed on the 7th, 3, 6 and 12 months subsequent to the surgery. In addition, the double-blind policy is maintained since the application of investigational device is performed by the expert who has a medical expertise and technique on the surgery and the application of investigational device, and the evaluator couldn’t know about the rule of random assignment and the allocation of subject to the group since the evaluator isn’t involved to the application of investigational device.

(2) Random Assignment of Subjects

In this clinical trial, random assignment was used to reduce bias that could be involved in the assignment of EG and CG, and to enhance the effects of comparison. To compare the precise difference in the range of motion of patient who underwent the partial mastectomy or total mastectomy, the subjects are assigned to each group randomly in similar proportion.

Our random assignment method is the block random assignment performed after generating random numbers (upto 4 places of decimals) for each subject using Excel’s random function (RAND). The sealed assignment slip is distributed to the subject. The sponsor of clinical trial provides the blinded slip which the investigational group or control is written down according to the randomly assigned subject table.

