**15-2 Safety Criteria Analysis**

(1) Adverse Events

All the AE that developed during the study period were analyzed. Their onset rate, the onset rate of AE that caused dropout, and the onset rate of SAE were summarized by group. They were coded using WHO-ART, then tested through the Chi-square test or Fisher’s exact test. The onset rates of AE were suggested as: onset rate of all adverse events, and the onset rate associated with the investigational device.

(2) Laboratory Tests

In the case of baseline continuous data from the laboratory test, descriptive statistics quantity (such as mean, SD, median, minimum, and maximum) was calculated, and their normal distribution was tested, then the difference between the groups was compared using One side, Two sample student t-test. In the case of categorical data, their descriptive statistics quantity (frequency and percentage) was suggested, and the difference between the groups was compared using the Chi-square test or Fisher’s exact test. After checking the investigational group’s test value came out on preoperative day and the 7th day following the surgery is different from it of control, we checked whether this difference is included within the normal error range or not.

1) Assessment of Criteria: Adverse events (Visit2, Visit3, Visit4, Visit5) and Hematologic Tests (Visit1, Visit2)

2) Evaluation criteria: The safety of investigational device is considered to be confirmed if the difference between the investigational group’s result value and control’s result value isn’t significant.

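### Dropout is defined by having received the device, which controls never do, so the planned by-group rate of adverse events causing dropout is zero in controls by definition

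*Protocol*

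**What the plan says.** Section 13-3 of the protocol is the only place that defines dropout: "Dropped out means a subject who was applied with the investigational medical device at least once, but he/she could not complete the clinical trial process".

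The control arm receives nothing. Section 10.2 explains that "we couldn’t find the reference medical device and didn’t assigned any medical device as the control" and takes the view that "it is safe to apply nothing to the surgical site". The arm listing in section 10.3 reads "CG: Not applicable".

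Sections 15-2 (1) and 16-1 (1) both plan a by-group summary that uses the term: "the onset rate of AE that caused dropout, and the onset rate of SAE were summarized by group". Both name the Chi-square or Fisher's exact test for the adverse event comparison. Section 15-2 then gives a decision rule under which the "safety of investigational device is considered to be confirmed if the difference between" the two groups is not significant.

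Section 8-3 treats dropout as something that happens in both arms: "Suppose that the 10% subject is dropped out in the middle of trial, the necessary total subject is 192 persons". Its table goes from 86 to 96 in the experimental group and likewise in the control group.

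Section 15-3 puts a similar device-use condition into the ITT definition, which admits subjects who used the device at least once after randomisation. It says that safety is basically analysed on that set.

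**The concern.** A dropout rate compared between arms needs one definition that subjects in either arm can meet. The definition in section 13-3 can be met only in the device arm. A control who leaves the trial because of an adverse event is not a dropout on the written wording, so that event cannot enter the control numerator. A device-arm subject who is randomised but not treated also falls outside the definition, although this should be rare because section 10.3 places assignment after the operation.

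At stake is one of the stated adverse event summaries. An analyst who follows the protocol compares the device arm with a structural zero. An analyst who counts control withdrawals anyway departs from the protocol's own definition and, if that choice is made after seeing the data, makes an unplanned choice in a safety comparison.

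**Working it through.** **1. The plan's own figure.** Section 8-3 uses "Significance level α = 0.025", power 90%, SD 10 and a distance of 5 between assumed difference and margin (10 − 5 or 15 − 10).

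- Normal approximation, one-sided: n = 2 × (1.960 + 1.282)² × 10² / 5² ≈ 84.1, so 85 per arm.
- The protocol's 86 is consistent with this. At 86 per arm the noncentral t power is 0.9032, which matches the 0.90323 in the protocol's table.
- Dropout: 86 / 0.90 = 95.6, so 96 per arm and 192 in total.

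The sample size reproduces. It allows 96 − 86 = 10 losses in each arm, controls included.

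**2. The definition applied to each arm.**

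- Device arm, treated as assigned: the condition of at least one application is met, so non-completion counts as dropout.
- Control arm, treated as assigned: no application takes place (10.2, 10.3), so the condition fails and non-completion never counts. Only a control given the device in error could qualify.

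Section 8-3 therefore allows for up to 10 control dropouts, while section 13-3 permits none.

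**3. Effect on the by-group rate.** The protocol gives no rate of adverse-event-caused dropout, so k below is an assumption. Let k of 96 subjects in *each* arm truly leave because of an adverse event. If both arms are counted, the table is k/96 against k/96. Under section 13-3 it becomes k/96 against 0/96. With equal arms and one zero cell, the two-sided Fisher value for the second table is

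p = 2 × C(96, k) / C(192, k).

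| k per arm (assumed) | Rate | p, both arms counted | p, controls forced to 0 |
| --- | --- | --- | --- |
| 1 | 1.0% | 1.00 | 1.00 |
| 2 | 2.1% | 1.00 | 0.50 |
| 3 | 3.1% | 1.00 | 0.25 |
| 4 | 4.2% | 1.00 | 0.12 |
| 5 | 5.2% | 1.00 | 0.059 |
| 6 | 6.3% | 1.00 | 0.029 |
| 10 | 10.4% | 1.00 | 0.0015 |

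Check at k = 5: 2 × (96·95·94·93·92) / (192·191·190·189·188) = 2 × 0.0296 = 0.059.

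The last row would apply only if every one of the 10 planned losses were caused by an adverse event. Section 13-4 lists other causes, including withdrawn consent and loss to follow-up, so that row is an upper bound within the planned 10%.

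**The case against.** The strongest reply is that section 13-3 is a careless sentence which the rest of the protocol overrides. Section 8-3 allows for control dropout, the withdrawal criteria in section 13-4 make no distinction by arm, and a by-group rate in sections 15-2 and 16-1 presupposes that controls can drop out. This is good evidence about intent. It does not repair the text, because no other section redefines the term. It shows instead that the protocol contradicts itself.

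A second reply is that the 0/96 illustration is selectively literal. Section 15-3 bases safety on a set also defined by device use. Read just as literally, controls are missing from the denominator too, and there is no control rate to test. That is fair, and it means both definitions have to be corrected together. On neither reading does the text yield a usable control rate.

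A third reply concerns consequence. The bias runs against the device, so it cannot produce a false finding of safety. The rate is one line within the adverse event summary: section 15-2 names adverse events and haematology as its criteria and does not say whether this rate alone would trigger the rule. With 5 or fewer such events per arm, the artefact does not reach the two-sided 0.05 level. All of this stands and limits the weight of the point.

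A reader might infer that control losses go unrecorded, so that differential attrition over 12 months could not be judged. The documents do not support this. In section 13-5 the term dropout governs the opening sentence of item 1 and the no-replacement rule in item 4. The duties to record reason, date, results and progress are written for withdrawal, or for subjects generally. Control withdrawals would still reach the CRF.

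**Conclusion.** The point holds as a contradiction of definition with a limited effect. Under section 13-3 a control treated as assigned cannot be a dropout. This conflicts with the 10% allowance for controls in section 8-3 and makes the by-group rate in sections 15-2 and 16-1 zero in controls by construction.

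The direction is certain: against the device. The size is not known. On assumed equal counts, the forced zero would turn no difference into a two-sided p below 0.05 from 6 of 96 per arm upwards, and would not do so at 5 or fewer. These figures assume 96 per arm and controls kept in the denominator.

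The point does not extend to the sample size, which reproduces. Nor does it extend to the primary range-of-motion endpoint: the missing-data handling in section 15-3 covers subjects who stopped participating as well as those who dropped out, so it does not turn on the section 13-3 wording. The protocol should be corrected, but this does not threaten the trial's main conclusion.

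**What to change.** - **Section 13-3:** define a dropout as any randomised subject, in either arm, who does not complete the trial for any reason.
- **Sections 15-2 and 16-1:** state that adverse-event-caused dropout is reported by assigned arm, with all randomised subjects as the denominator.
- **Section 15-3:** remove the device-use condition from the ITT definition, so that controls are in the safety denominator. Changing section 13-3 alone would leave that gap.

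The cost is a few sentences in one amendment. It needs no new visits, measurements or subjects, because sections 13-4 and 13-5 already have withdrawals and their reasons recorded without regard to arm.

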**13-4. Withdrawal Criteria**

(1) The clinical trial can be withdrawn if the required tests cannot be conducted due to subject conditions or other reasons.

(2) The clinical trial can be withdrawn if subjects show serious AE, adverse device effect (ADE), or serious AE (SAE), which make it difficult to continue with the clinical trial.

(3) The clinical trial can be withdrawn if a serious offence of the protocol develops.

- The clinical trial can be discontinued due to the offence of the inclusion criteria, which can affect the efficacy evaluation.

(4) The clinical trial can be withdrawn if the subjects or legally authorized representatives want discontinuation through withdrawal of the written consent.

(5) The clinical trial can be withdrawn if subjects are not followed up.

(6) The clinical trial can be withdrawn if investigators determine it should be

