**13-5. Process of Withdrawal**

(1) Dropout cases must be appropriately managed and treated, and the development must be observed and recorded. The reason of withdrawal must be recorded in the CRF.

(2) All the test results up to the time of withdrawal, the date, reasons, treatments and progress at the time of withdrawal must be recorded in the CRF.

(3) If subjects do not show up for a visit, mail, interview, and phone calls can be used to investigate the reasons and progress, and the results are recorded in the CRF.

(4) The dropout subjects are not replaced with new subjects.

(5) If subjects withdraw in the middle of the clinical trial, they are not required to explain the reason, but investigators must try to confirm the reason upon considering the subject rights.

(6) If there is an outcome of efficacy and safety evaluation (such as AE and concomitant medication) at the time of withdrawal, it must be included in the analysis unless this distorts the validity of the clinical trial.

(7) The result of pregnant subject can be collected only for ethical purpose and the observation on that subject will be continued even after the drop-out.

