**15-3 Statistical Analysis**

(1) Methods: One side, Two sample student t-test, Chi-square test, Fisher’s exact test

(2) Main analysis: ITT analysis

(3) Additional analysis: PP analysis

(4) Statistical power: 80%

* When performing the statistics for effectiveness evaluation, the information of subject who stopped to participate in or was dropped out from clinical trial is excluded from the compliance group (per protocol group) and is dealt as a missing value when the subject is assigned to the analysis group according to assignment table.

(5) General Principals of statistical analyses

The subject data of this study were analyzed through ITT (Intention to Treat) analysis and PP (Per Protocol) analysis.

In the ITT analysis, all the data obtained from the subjects who used the investigational device at least once after they were randomly assigned to the group were used. The above-mentioned subject’s information is excluded from the analysis for primary and secondary the missing value at the primary and secondary is discovered.

In the PP analysis, ITT analysis was data obtained from the subjects who completed the clinical trial according to the protocol were included. And the above-mentioned subject’s safety endpoint shall be included in ITT group. The value of subject which is out of clinical trial’s policy critically and may affect the efficacy evaluation (Exclusion criteria 2. The subject who is diagnosed as a breast cancer, absent on visit 1 and 2(each), assigned to the incorrect group, and experiences the severe adverse events during the clinical trial) will be included in the ITT group analysis with being excluded from the PP group analysis.

The efficacy evaluation was conducted using The efficacy evaluation was conducted using the ITT and PP analysis as a main method, while the PP analysis was used as an auxiliary method when the analysis results were inconsistent. The results of both analyses were compared. Demographical evaluation and safety evaluation were basically analyzed through the ITT analysis.

(6) Demographical Data

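### Investigators may withdraw subjects after a one-time intra-operative treatment, and nothing secures their 3-, 6- and 12-month outcomes, although the main ITT analysis is said to keep them

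*Protocol*

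**What the plan says.** **Treatment.** Section 10.3 (1) of the protocol states that "the investigational device is applied inside of subject in the middle of surgery under anesthetic". The Clinical Trial Schedule marks the device only immediately after surgery. Post-operative range of motion, DASH and pain are measured at Visits 3, 4 and 5 (3, 6 and 12 months).

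**Withdrawal.** Section 13-4 (3) says "The clinical trial can be withdrawn if a serious offence of the protocol develops" and adds "The clinical trial can be discontinued due to the offence of the inclusion criteria, which can affect the efficacy evaluation". The wording speaks of the trial, but the section heading and 13-5 show that withdrawal of the individual subject is meant. Item (2) allows withdrawal for serious events that make continuing difficult, and item (6) allows it whenever investigators so decide. Section 13-6 leaves continuation after a violation to the investigators, who are to weigh its effect on the device's efficacy and safety.

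**Data after withdrawal.** Section 13-5 (2) says "All the test results up to the time of withdrawal, the date, reasons, treatments and progress at the time of withdrawal must be recorded". Item (6) brings an outcome available at withdrawal into the analysis, with an exception where it would distort validity. Item (7) says "The result of pregnant subject can be collected only for ethical purpose and the observation on that subject will be continued even after the drop-out".

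**Analysis.** Section 15-3 makes ITT the main analysis. Subjects with a critical violation, including wrong-group assignment and severe adverse events, "will be included in the ITT group analysis with being excluded from the PP group analysis". The same section treats data of stopped or dropped-out subjects as missing and leaves subjects with missing endpoints out of the primary and secondary analyses.

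**The concern.** In a trial of continuing treatment, withdrawal can at least end exposure. Here exposure is complete before the first follow-up visit, so an investigator-decided withdrawal removes only the outcome.

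The grounds for withdrawal in 13-4 and 13-6 overlap with the categories that 15-3 says belong in ITT. A subject withdrawn on one of these grounds before Visit 3 has a place in the main analysis by name but no post-operative value to put there.

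The loss need not be random. The title claims blinding of subject and assessor only, and under 10.3 the device is applied by surgically trained staff who therefore know the arm. Section 13-4 (6) sets no criterion and does not require the decision to be made blind to arm. Section 13-6 makes the expected effect on efficacy a stated consideration. Values never measured cannot be fully recovered by any analysis method, so this cannot be left to a statistical analysis plan.

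**Working it through.** **1. The sections side by side**

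| Subject | Participation (13-4, 13-6) | ITT (15-3) | Visits 3 to 5 secured after withdrawal? |
|---|---|---|---|
| Serious protocol violation | may be ended | kept | no |
| Inclusion-criteria violation | may be ended | kept if critical | no |
| Wrong group | may be ended, as a violation | kept | no |
| Severe adverse event | may be ended if serious and continuing is difficult | kept | no (the event itself is followed, 16-5) |
| Investigator judgement | may be ended | treated as missing | no |

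**2. The plan's own figures.** Inputs from 8-3: one-sided alpha 0.025, SD 10, 1:1 allocation, margin 10 and true difference 15 (5 degrees beyond the margin). The noncentral t distribution gives 90.32% power at 86 per arm, which matches the table entry 0.90323. With 10% dropout, 86 / 0.9 = 95.6, rounded up to 96 per arm. The figures reproduce.

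The 10% allowance is fully used by this. Investigator-decided withdrawals come out of the same allowance as unavoidable losses. With an assumed 20% total loss, 76 per arm remain and power is 86.5%.

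**3. Bias from one-sided loss.** All counts and deficits here are assumptions. Suppose k of 96 device subjects are withdrawn, and their mean would have been x degrees below the full-arm mean. The mean of those remaining is then too high by

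shift = k·x / (96 − k).

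Take k = 5, no controls lost, and a true difference exactly at the 10-degree null boundary. The standard error is 10·√(1/91 + 1/96) = 1.463 and the critical t (185 df) is 1.973.

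| Deficit x | Shift | Shift / SE | One-sided error (nominal 2.5%) |
|---|---|---|---|
| 5 | 25/91 = 0.27 | 0.19 | 3.8% |
| 10 | 50/91 = 0.55 | 0.38 | 5.6% |
| 20 | 100/91 = 1.10 | 0.75 | 11.3% |

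With 91 in both arms for simplicity, the last figure is 11.1% and the others round to the same values.

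**4. How extreme these cases are.** In normal samples of 96 with SD 10, the five lowest values average about 20 degrees below the mean (checked by simulation). The 20-degree row therefore amounts to losing exactly the five worst device subjects. If 5 device and 3 control subjects are lost at 20 degrees, the shift is 100/91 − 60/93 = 0.45 and the error is 4.9%. If 5 are lost from each arm with equal deficits, the shift is zero and the error stays at 2.5%. Selective loss in the control arm would bias the comparison against the device.

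**The case against.** Much can be said for the protocol as written.

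- **Withdrawal is permitted, not ordered.** Every item in 13-4 is discretionary, item (2) is limited to serious events that make continuing difficult, and 13-6 names continuation as an option. A reader might infer that these outcomes are certain to be lost. The documents do not support that. What stands is that the discretion has no criteria and that nothing preserves the outcomes once it is used.
- **Safety follow-up does not simply end.** A reader might infer that the patients with the worst events are no longer followed. Section 16-5 requires follow-up of existing adverse events until they resolve or are explained, and 13-5 (1) requires a dropout's course to be observed and recorded. Only the fixed visits lapse, and with them the scheduled detection of new events.
- **Pregnancy is not abandoned.** Sections 13-5 (7) and 16-9 continue observation. Neither says that goniometry, DASH or VAS is done at the planned times, and the subject still counts as a dropout.
- **Section 15-3 foresees dropouts as missing.** It would be too strong to call 13-4 and 15-3 flatly contradictory, because violators who are not withdrawn can be analysed as stated. The conflict arises when the discretion is exercised.
- **Eligibility errors and wrong-arm application have no stated link to poor motion.** For such subjects the bias may be small.

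Mail and telephone contact (13-5 (3)) and outcomes available at withdrawal (13-5 (6)) also help, but neither yields a goniometer reading at 3, 6 or 12 months.

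**Conclusion.** The point holds as a gap in outcome collection. After a single intra-operative application, the protocol lets investigators end participation and asks for results only up to that time. It then treats as missing subjects whom it also assigns to its main analysis.

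The harm falls mainly on the efficacy endpoints, and secondarily on scheduled detection of new adverse events. Its size depends on how often the discretion is used and how unevenly, which the documents cannot show. With five device subjects lost and no controls, the one-sided error ranges from 3.8% to about 11% for deficits of 5 to 20 degrees. The upper end is close to a worst case and should not be read as an expected value. Balanced losses leave no bias and cost only power. That the operating team's knowledge of the arm could influence withdrawal is a possibility the rules leave open. The documents do not say who would take the decision or whether that person is blinded. The change should be made because it is cheap and removes an avoidable source of selective missing data.

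**What to change.** In 13-4, 13-5 and 13-6, state that a protocol or eligibility violation, a wrong-arm application, an adverse event or a pregnancy does not by itself end outcome collection. State that Visits 3 to 5 continue for all assessments that are feasible and to which the subject consents. Record the event or violation in the CRF, analyse the subject as randomised in ITT, and handle violations through the PP set only. Reconcile these sections with 15-3.

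Consent withdrawal, loss to follow-up and the case where required tests cannot be done (13-4 (1), (4) and (5)) can remain. The change concerns data collection only and leaves clinical care to the investigators.

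The cost is a wording amendment. The visits are already in the schedule, so the only downside is that a few more of them are carried out.
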